#### Qualitative data

We will conduct qualitative data collection in three stages: pre-intervention, midline and post intervention qualitative data collection. For each of the stages, we will conduct focus group discussions (FGDs), in-depth interviews (IDIs) and key informant interviews (KIIs) as well as observation of care provision to assure quality of services. The number of interviews per stage and sub-group to be interviewed as well as the sample size will mainly depend on the level needed to achieve saturation of concepts. However, we anticipate the following number of interviews per stage: 8 IDIs, 8 FGDs, and 14 KIIs per county. We expect that each FGDs will have 8 people. Table 6 gives an overview of the sample size for qualitative data collection.

**Table 6 Tab6:** Summary of proposed KII, IDI and FGDs, in each county (Turkana and osiolo)

Method	Participants	Interviews/discussion sessions	Participants (#)	Total discussion sessions (#)
IDIs	Mothers			
	• In program, • Not in the program • Defaulters	8	1	8
		8	1	8
		8	1	8
FGDs	Mothers	1	6	6
	Men (fathers)	1	6	6
	Grandmothers	1	6	6
	CHW	1	6	6
KII	Community leaders & others	6	1	6
	Health professionals • Doctors, Nurses & nutritionist	2	1	2
	County and national level CHMT and Policy/decision makers	2	1	2
	Implementing partners (ACF/Save the children)	2	1	2
Total				60

For the qualitative data collection, purposive sampling will be used to sample women of reproductive age with children suffering from acute malnutrition, fathers of children being treated for acute malnutrition, other community members including grandmothers, health care providers, community leaders and policy/decision makers in the Ministry of Health, County health management teams, county executive officer, county director of health, implementing partners and other key organizations in the study areas.

### Pre-implementation qualitative data collection stage (baseline)

Rapid qualitative methods including in-depth interviews, FGDs and KII will be conducted with various stakeholders. Targeted women will be those whose children have been /are being treated for acute malnutrition or are suffering from acute malnutrition, their spouses and other men whose children have been treated/are being treated for malnutrition, other stakeholders including implementing partners, Ministry of Health officials, County government and local community leaders.

The qualitative study will seek to answer questions regarding general knowledge attitude and practices with regards to child feeding and current treatment of MAM/SAM, challenges that hinder treatment of acute malnutrition, cost and time implications of the new model of treatment, and the barriers and facilitators that affect the MAM/SAM treatment outcome measures including average length of stay; average rate of weight gain; cure rate; mortality rates; default rates and transfer rate. The study will also qualitatively seek to establish the views of CHVs and other health workers on the effect of the integration of iCCM and management of acute malnutrition (SAM and MAM) on their workload as well as its likely effect on the quality of standard iCCM care. For the implementing partners, policy and decision makers, we will focus mainly on their recommendations for adaptation of the integrated program and their perceived role in it.

#### Implementation phase qualitative data collection

During the implementation phase, qualitative data will be collected at mid-term whereby we will conduct in-depth interviews, key informant interviews and focus group discussions with women/ caregivers in the program, on their experiences with the integrated package and their satisfaction as well as suggested potential areas of improvement. We will also conduct focus group discussions with CHWs and key informant interviews with other stakeholders (implementing partners and the Ministry of Health Officials including the CHMT and Health Facility Workers) on their views on the progress of the integrated program including facilitating and limiting factors, and the cost and time implications of the intervention. The information gathered will be useful in engaging the stakeholders including the implementing partners, the Ministry of Health, UNICEF and WFP during the remaining section of the implementation phase in order to minimize potential risks and counter challenges experienced and to maximize on the potential benefits.

#### Post-implementation qualitative data collection

We will conduct qualitative interviews among women whose children were treated for acute malnutrition during the implementation period, and men (fathers of the children) as well as other community members to assess their experience and satisfaction with the integrated program within the period of the implementation, and potential areas of improvement, observed advantages and challenges and perceived effects of the integrated program including adherence to the treatment given, recovery rate and their relationship with the CHVs during the implementation phase. We will also conduct interviews with the CHVs to determine their experiences in implementing the integrated package including challenges and facilitators; their views on its effect on their workload; effect on the quality of care given; their views on their capability to administer treatment; and their suggestions on the possible areas of improvement.

### Training of research assistants and piloting

Data will be collected by qualified and well trained data collectors in line with APHRC’s training requirement. Qualitative data collection will be undertaken by trained field interviewers with college or higher level of education (preferably in nutrition or health related field) and with previous experience in qualitative data collection in arid and semi-arid lands. Quantitative data will be collected by carefully trained field workers with a college certificate and previous experience in quantitative and qualitative data collection. All field workers will be expected to be fluent in both English and Swahili and the local language with a preference given to interviewers residing in or near the study area. After recruitment, research experts on the different methods of research as detailed above from within the team will conduct a week-long training of field interviewers on ethics for research with human participants, data collection procedures, ensuring good quality data, and reporting. Consistent check-ins with the interviewers will be used as an approach to ensure high quality data is captured.

### Management of data quality during field work

To ensure that high quality quantitative data is collected, validation rules, constraints or checks (skips) in the questionnaire will be embedded within the data collection electronic software during programming of the tool. This will allow the interviewers to quickly notice missing data and implausible or out of range values. The data collection program will also be tested severally prior to data collection. Regular spot checks by the project team with field interviewers, and an automated routine check on data completeness and discrepancies will also be implemented to enhance data quality. Interviewers will be responsible for following-up on any inconsistencies or errors in the data with their participants as/when needed.

To ensure that high quality qualitative interviews are conducted, the research team will sit-in on a select number of interviews, also regularly review the data collected for quality. Regular debriefing sessions with the interviewers will also ensure that emerging ideas are followed-up on in subsequent interviews. In addition, transcripts will undergo data verification by checking them to confirm accuracy against the original audio-recordings.

### Data processing and analysis

#### Quantitative data management, storage and analysis

In a non-inferiority in CRCT, we will first analyze the findings using non-parametric namely the adjusted Chi-squared test for clustered binary such as recovery rate, case fatality and defaulter rate. For continuous outcomes, we will use t-test for clustered data namely for weight gain. Furthermore, for our primary outcome we will use an econometric model namely a Probit model where the dependent variable is the recovery rate and covariates are the treatment variable (one for the intervention and zero for the control), age of the children, gender of the children, vaccination status (unvaccinated, partially vaccinated, fully vaccinated), overall length of stay, breastfeeding, co-morbidities at admission (malaria, anemia, pneumonia, measles and giardiasis), admission status (new admission, readmission, admission after default), education of the mothers, income of the mothers etc.

All digital project data will be stored in encrypted computers or laptops that are password protected, with regular back-up procedures to the server put in place to ensure that the data is not lost. All survey data will be collected via password protected tablets and uploaded to a secure cloud-based data depository after completion of the survey. Data will then be deleted from the tablets. Non-anonymized data will be stored on a secure, password projected server made accessible only to the core research team. All data will be anonymized before being made available to other project staff, ensuring the confidentiality of data following collection.

Quantitative data will be analyzed using STATA, SPSS and/or MLWin files. Prior to data sharing, it will be anonymized. The primary aim of the analyses conducted will be to answer the research questions outlined in the protocol. Quantitative data analysis will mainly be descriptive. Qualitative interviews will be audio-recorded on encrypted recorders, transcribed verbatim (and translated/transcribed as needed), anonymized and stored in digital format (MS Word compatible).

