### Intervention protocol

#### Criteria for admission

At admission, the CHVs will only screen under five children (aged 6–59 months) and carryout preliminary examination for any danger signs. This will be followed by further examination for complaints including cough/cold, diarrhea, dehydration and fever, which will be followed by anthropometric measurements to classify the child in relation to nutritional status either MAM, SAM or normal. A special five color-band MUAC tape will be used to allow identification.

Children with MUAC < 9.5 cm and/or less than 4 kg on the dosage scale, with/without bilateral pitting oedema, those who fails the appetite test or show presence of iCCM danger signs or other illnesses other than iCCM diseases (diarrhoea, malaria, pneumonia), sick neonates (less than 1 month) and malnourished children less than 6 months, will be subject for referral to the health facility. However, those sick children below 2 months and caregivers who fail to consent will be excluded at the recruitment and only referred to the health facility.

If MUAC is < 11.5 cm, the child will be classified as SAM; before admitting the child directly for treatment, do the following: children presenting a MUAC of < 11.5 cm will be defined as with SAM while MAM will be defined as MUAC of between 11.5 cm and 12.5 cm. The CHVs will then conduct physical examination of MAM and SAM cases. At this stage, examination for any oedema not observed during assessment of danger signs will be detected. Appetite test will then be conducted setting the stage for either referral or exclusion. Wait for up to 30 min before deciding the child has poor appetite. If the child takes significant quantities as indicated in the Table 3, interpret as the child has good appetite. If no complications and good appetite, the child will be admitted for community-based management of malnutrition.

**Table 3 Tab3:** Appetite test interpretation

Weight (kg)	Sachet portion the child needs to finish to pass appetite test
4–6.9	1/4 to 1/3
7–9.9	1/3 to ½
10–14.9	1/2 to ¾
15–29	3/4 to 1

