#### Follow-up stage

At follow-up, CHVs will ask and seek for general danger signs and examine any complaints on the child. In addition, the systematic evaluation will be conducted to examine any cough, fever or diarrhea following the standard treatment and follow-up protocol. Anthropometric measurement weight and MUAC will be taken to determine any changes (gains) in the child. The CHVs will further conduct systematic evaluation to look for edema not detected at the general danger signs and appetite test. Children with either danger signs, failed appetite test, weight loss, diarrhea will be referred to the health facility, otherwise the CHVs will conduct treatment for MAMA or SAM as appropriate.

For SAM cases, during follow-up the RUTF will be provided for the next 7 days and if RDT is positive, ACT will be provided on the spot and twice daily for 3 days. Adelbanzole will be given if during the second visit the child is aged more than 12 months. In the case of MAM, the CHVs will give folic acid and continue RUSF for the next 7 days. The diversification and breastfeeding should be emphasized again at this point.

Furthermore, during follow-up all SAM children will be subject to weekly visit to CHVs for MUAC measurement and weight using the dosage scale, and collection of RUTF as per dosage scale will continue for a maximum of eight weekly visits if the child is progressing well, otherwise referral will be recommended in case of non-response to treatment. On the other hand, MAM children will be subject to bi-weekly (every 2 weeks) visits for MUAC measurement and collection of RUSF (1 sachet per day for 16 weeks for a maximum of eight visits if child is progressing well, otherwise the child needs to be referred). Table 5 outlines the follow-up procedure for both MAM and SAM.

**Table 5 Tab5:** Follow-up procedure for both MAM and SAM

Follow up	Discharge criteria		Action
1) SAM, MUAC < 11.5 cm			
Weekly visit to CHV for MUAC measurement and weight using the dosage scale and collection of RUTF as per dosage scale Maximum of 8 weekly visits if child is progressing well Two consecutive MUAC and/or weight measurements with no change or deterioration	cured	MUAC≥12.5 cm 2 consecutive green on MUAC	Discharge as cured
	defaulter	Misses 3 consecutive visits	Exclude from the study, Trace and admit as return defaulters but not for study

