### Data collection procedures

#### Quantitative data

Quantitative data will be conducted at baseline to establish coverage of SAM and MAM treatment as well as other relevant nutrition and iCCM indicators. Data on treatment outcomes will be collected during the implementation. Further, end line quantitative data collection will be done to assess the coverage of SAM and MAM treatments as well as other relevant nutrition and iCCM indicators.

These data will be collected via quantitative household surveys. Building on our extensive experience with household nutrition surveys and iCCM, We shall use questionnaires to collect detailed information on socio-demographic and economic characteristics of the household, child characteristics including health, nutrition status and standard anthropometrics in every time period. Anthropometric data, will include child’s weight, presence of oedema, height and mid-upper arm circumference will also be collected, using standard protocol [19]. Additionally, CHVs will also be interviewed to obtain data that shall inform of their understanding and practice of the laid out protocol. The same information will be compared with data collected from mothers or caregivers of children in the clusters to gauge the treatment regime received compared to the laid out practice. Altogether an understanding of the effectiveness of this service will be obtained. These questionnaires to be used will be pre-tested before fielding the final survey. Furthermore, in the Kenya context, at the level of health facility, there are registers which are used to follow-up children with MAM/SAM cases. Those registers provide valuable information on the outcomes (recovery, defaulter and death). But, for the community-based management of malnutrition, we will use similar registers to record all the management of MAM/SAM cases which will also provide information on our outcomes. We will setup a tracking system which help us to randomly select our sample size of MAM/SAM cases and follow-up them till 4 months period at each time point.

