## APPENDIX

### Sample size calculation for non-inferiority cluster randomized controlled trials

We follow Rutterford et al. [35]‘s study for sample size calculation of non-inferiority in CRCT. In the current study, we assume that the integration of CMAM into iCCM will yield a recovery rate of 75% and there is truly no difference between the standard (CHV *are not* treating MAM/SAM cases) and experimental treatment (CHVs *are treating* MAM/SAM cases) in terms pf recovery rate. We assume an intracluster correlation (ICC) of *ρ* = 0.005, one-sided 95% confidence interval, a power of 80%, cluster size of 24 cases of MAM/SAM, and an attrition rate of 5%. Lastly, we assume a non-inferiority limit (*d*) **to be 15%.**

Hence, the following formula of the sample size with binary data is:

1 $$ N=\frac{{\left({Z}_{1-\frac{\alpha }{2}}+{Z}_{1-\beta}\right)}^2\left\lfloor {\pi}_s\left(1-{\pi}_s\right)+{\pi}_e\left(1-{\pi}_e\right)\right\rfloor }{{\left({\pi}_s-{\pi}_e-d\right)}^2}\left\lfloor 1+\left(m-1\right)\rho \right\rfloor $$

with, $$ {Z}_{1-\frac{\alpha }{2}} $$ and *Z*_1 − *β*_ the values from the normal distribution holding $$ 1-\frac{\alpha }{2} $$, 1 − *β* below it, respectively. *α* and *β* are levels of significance and power, respectively. Where *π*_*s*_ and *π*_*e*_ are the recovery rate in the standard and experimental treatment group, respectively. *ρ*, *m* and *d* are the ICC, cluster size and non-inferiority limit**,** respectively.

If we further posit that *π*_*s*_ = *π*_*e*_ = 0.75, Eq. (1) becomes:

2 $$ N=\frac{{\left({Z}_{1-\frac{\alpha }{2}}+{Z}_{1-\beta}\right)}^22{\pi}_s\left(1-{\pi}_s\right)}{(d)^2}\left\lfloor 1+\left(m-1\right)\times \rho \right\rfloor $$

Using Eq. (2), the total sample size is:

$$ N=\frac{{\left(1.64+0.84\right)}^2}{(0.15)^2}2\times 0.75\left(1-0.75\right)\left\lfloor 1+\left(24-1\right)\times 0.005\right\rfloor $$

$$ N\approx 114.29 $$

If we assume an attrition rate of 5%, then:

$$ {N}_{CRCT}=\frac{114.29\ }{1-0.05}\approx 120 $$

The total number of cluster per arm is:

$$ {N}_{CRCT}=\frac{120\ }{24}=5 $$

We will therefore recruit 120 MAM/SAM cases for each group. The cluster size of children in each of the five equally sized clusters per arm is 24 children per clusters. This process will be done at the baseline (240) and endline (240).

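### Average weight gain, a listed primary outcome, is compared only by an unadjusted clustered t-test; adjusting for age, admission weight and SAM/MAM class would be a cheap gain in precision

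*Protocol article*

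**What the plan says.** The Primary outcomes section of the protocol article lists seven items, one of them average weight gain. The sample size section and the Appendix use recovery alone as the sizing outcome. No target difference, standard deviation or margin is given for weight gain.

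Under Quantitative data management, storage and analysis, the test for weight gain is named: "For continuous outcomes, we will use t-test for clustered data namely for weight gain". The only covariate model in the article follows directly: "for our primary outcome we will use an econometric model namely a Probit model where the dependent variable is the recovery rate". Its covariates begin with "age of the children, gender of the children, vaccination status". No adjusted model is named for weight gain.

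The relevant baseline variables are already in hand. Criteria for admission provides for "anthropometric measurements to classify the child in relation to nutritional status either MAM, SAM or normal", and the RUTF dosing chart requires the child's weight. Follow-up stage says: "Anthropometric measurement weight and MUAC will be taken to determine any changes (gains) in the child". Weight gain cannot be computed in either arm without an admission weight, and age is both an eligibility item and a Probit covariate. (The anthropometry described under Quantitative data belongs to the household survey, so it is not the best evidence for admission records.)

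**The concern.** The arms pool children aged 6 to 59 months, in weight bands from 4 kg to 12 kg and above. SAM and MAM children are given different products on different visit schedules. Weight gain can be expected to vary with age, size and severity whichever arm a child is in. An unadjusted comparison counts all of that variation as noise.

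With five community units (CUs) per arm, chance differences in age or in the share of SAM cases are also plausible, and they would pass straight into the estimate. The article's own survey figures show that case mix varies by place: SAM is 5/21.2, about 24%, of global acute malnutrition in Turkana and 0.4/3.8, about 11%, in Isiolo.

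At stake is a wider confidence interval for a listed primary outcome than the collected data would allow. The validity of the test and the size of the trial are not in question.

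**Working it through.** **The plan's own figure.** Appendix Eq. (2): (1.64 + 0.84)² × 2 × 0.75 × 0.25 / 0.15² × (1 + 23 × 0.005) = 114.29 per arm. Then 114.29/0.95 ≈ 120, and 120/24 = 5 CUs per arm. This reproduces. It concerns recovery only, so nothing below changes the planned sample size.

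**Inputs for weight gain.**
- From the article: 5 CUs per arm, 24 children per CU, 5% attrition (120 × 0.95 = 114 per arm), ICC 0.005, hence design effect 1 + 23 × 0.005 = 1.115.
- Assumed: the same ICC applies to weight gain; two-sided 5% test; unmatched comparison with 10 − 2 = 8 df; SD = 1 unit; rho, the multiple correlation between weight gain and the covariate set, from 0.3 to 0.6.

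**Unadjusted detectable effect.** SE = √(2 × 1.115/114) = 0.1399 SD. The noncentral-t parameter giving 80% power at 8 df is 3.201. Detectable effect = 3.201 × 0.1399 = 0.448 SD.

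**After adjustment.** Residual variance is multiplied by (1 − rho²), so the noncentrality at 0.448 SD becomes 3.201/√(1 − rho²). At rho = 0.5 the variance falls by 25%, and the detectable effect falls to 0.448 × √0.75 = 0.388 SD.

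| rho | Variance ratio | Power, 8 df | Power, 7 df | Power, 6 df |
|---|---|---|---|---|
| 0 (unadjusted) | 1.00 | 80% | – | – |
| 0.3 | 0.91 | 83.5% | 82.0% | 79.7% |
| 0.4 | 0.84 | 86.3% | 84.8% | 82.7% |
| 0.5 | 0.75 | 89.8% | 88.5% | 86.6% |
| 0.6 | 0.64 | 93.7% | 92.7% | 91.2% |

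The 7 and 6 df columns charge one or two degrees of freedom for the covariates. At rho = 0.3 the gain is then about 2 points or nil.

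**Sensitivity.** In each case the comparison is at the effect that has 80% power unadjusted in that setting.
- *Covariates explain only within-CU variance.* Variance ratio = [ICC + (1 − ICC)(1 − rho²)/24] / [ICC + (1 − ICC)/24]. At rho = 0.5 and ICC 0.005 this is 0.777, power 88.7%. At an assumed ICC of 0.05 it is 0.0797/0.0896 = 0.890, power 84.3%.
- *Admission weight alone.* Gain already subtracts admission weight. With equal variances at both times, adding it as a covariate changes the variance by σ²(1 − r²)/[2σ²(1 − r)] = (1 + r)/2, where r is the correlation of admission and later weight. At r = 0.9 the ratio is 0.95 (power about 82%); at r = 0.7 it is 0.85 (about 86%). Unless r is low, most of the benefit must come from age and SAM/MAM class.
- *Twenty CUs.* Sampling procedures selects ten CUs in each county. With 228 per arm and 18 df, the detectable effect goes from 0.293 to 0.254 SD at rho = 0.5, with nearly the same power gains.
- *One-sided 5%, as in the sample size section.* Noncentrality 2.727 at 8 df. The detectable effect goes from 0.381 to 0.330 SD at rho = 0.5, and power rises from 80% to between 83.2% and 92.7% over rho 0.3 to 0.6.
- *Five matched pairs, 4 df, no variance credit for matching.* Noncentrality 3.761. The detectable effect goes from 0.526 to 0.456 SD at rho = 0.5, and power rises from 80% to between 83% and 93%.

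The absolute detectable effects depend on these choices. The relative gain depends mainly on rho and on how the variance splits between and within CUs.

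**The case against.** A t-test for clustered data respects the unit of randomisation and is a legitimate analysis. The article presents the simple tests as a first step, and as a condensed document it may leave further models to an analysis plan that is not shown. Recovery is the outcome that sizes the trial and the one the analysis section calls primary in the singular. With no power planned for weight gain, no planned power is lost. All of this stands, and it sets the priority. It does not remove the point, because the article names a specific test for this outcome and, in the same paragraph, adjusts recovery only.

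Two further objections also have force. The CUs are to be pair-matched on baseline data, which should reduce imbalance between arms. Matching acts on unit-level characteristics, though, and the endline children are a new cohort, so individual age and severity can still differ. Second, the pre-implementation qualitative section describes the measure as an average rate of weight gain. If it is a rate, the different maximum treatment periods for SAM and MAM are largely divided out and cannot be used as an argument for adjustment.

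A reader might infer that the t-test is biased, that the sample size is inadequate, or that about ten points of power are being lost. The documents support none of these. Chance imbalance is not bias, the sample size rests on recovery, and the ten-point figure depends on an assumed rho of 0.5.

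**Conclusion.** The point holds as lost efficiency, not as an error. A listed primary outcome is analysed without baseline variables that the trial already records, while recovery is adjusted. Under the main assumptions (10 CUs, unmatched, two-sided 5%, 8 df, ICC 0.005), adjustment raises power from 80% to between 83.5% and 94% for rho of 0.3 to 0.6. The lower end shrinks to about 2 points or nothing once one or two degrees of freedom are charged, and the whole range shrinks if between-CU variance dominates. Rho is an assumption throughout. This is a free or cheap improvement of low to moderate priority.

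**What to change.** In the quantitative analysis section, make the main weight-gain analysis a prespecified linear model with arm, admission weight, age and SAM/MAM class at admission. Admission MUAC may replace the class, but including both adds little because the class is defined mainly by MUAC. Use only variables known at admission. The Probit covariate list should not be carried over as it stands, since it includes length of stay.

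Respect the CU and the matched pairs. One way is in two stages: regress weight gain on the individual baseline covariates without arm, then run a t-test on the CU-mean residuals, paired if the matching is kept, with cluster-level degrees of freedom. State whether weight gain is an absolute change or a rate. Keep the unadjusted clustered t-test as a supporting analysis.

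The cost is a few lines of text and a little more analysis work, with no new data. A one-stage model may use one or two degrees of freedom.

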#### Inclusion/exclusion criteria

To be included in the study, the following criteria highlighted in Table 2 should be met.

**Table 2 Tab2:** Inclusion and exclusion criteria

CHVs Inclusion/ exclusion Criteria	Under-five Children Inclusion/ Exclusion Criteria
Inclusion criteria • CHVs who have been recruited and trained as CHVs by the MoH community strategy and willing to undertake and devote more of their time to the study	Inclusion criteria • Children 6 to 59 months presenting with SAM (a MUAC of < 115 mm or presence of bilateral pitting edema, without complications) or MAM (MUAC of 115 to 125 mm). • Parents/caretakers willing to participate in the study
Exclusion criteria • CHVs who have discontinued their community services or move out of the study area	Exclusion criteria • Parents/caretakers who are not willing to consent/ participate in the study.

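### The Probit model for recovery adjusts for length of stay, a post-allocation outcome, so its treatment coefficient is not the effect on recovery

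*Protocol article*

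**What the plan says.** All references are to the protocol article.

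- **Analysis section** (Quantitative data management, storage and analysis). Recovery is tested first without covariates: "we will first analyze the findings using non-parametric namely the adjusted Chi-squared test for clustered binary such as recovery rate". A regression follows: "for our primary outcome we will use an econometric model namely a Probit model where the dependent variable is the recovery rate". Its covariates are treatment, age, gender, "vaccination status (unvaccinated, partially vaccinated, fully vaccinated), overall length of stay, breastfeeding, co-morbidities at admission", and then "admission status (new admission, readmission, admission after default), education of the mothers, income of the mothers etc". The list is left open at the end.
- **Outcomes.** The Primary outcomes list contains the cured rate and the average length of stay as separate items. The section on pre-implementation qualitative data also counts "average length of stay" among the treatment outcome measures.
- **Exit rules** (Follow-up stage and Table 5). A child leaves when cured, on default, on non-response or when lost to follow-up. Otherwise the stay runs to a cap: for SAM a "maximum of eight weekly visits if the child is progressing well", for MAM eight visits at two-week intervals, which is 16 weeks.
- **Severity.** The trial enrols "SAM (a MUAC of < 115 mm or presence of bilateral pitting edema, without complications) or MAM (MUAC of 115 to 125 mm", and admission includes "anthropometric measurements to classify the child in relation to nutritional status either MAM, SAM or normal". Neither MUAC nor SAM/MAM class is among the named covariates.

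**The concern.** A covariate in a model for a treatment effect should be fixed before treatment can act on it. Length of stay is not. It accrues after allocation, and the protocol treats it as something the intervention may change. The conceptual framework expects earlier case-finding and earlier treatment, either of which could alter stay. Stay also depends on the outcome being modelled, since cure is one of the events that ends it.

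The plan therefore places one primary outcome on the right-hand side of the model for another. The resulting coefficient compares children in the two arms who happened to stay equally long. That is a different question from whether CHV treatment gives a recovery rate no more than 15 points below facility treatment. The Probit is the only named model that gives a covariate-adjusted effect on recovery, so its estimate is likely to be reported and read against the margin.

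**Working it through.** **1. The plan's own figure.** Inputs from Sample size estimation and the Appendix: recovery 75% in both arms, margin 0.15, z values 1.64 and 0.84, cluster size 24, ICC 0.005, attrition 5%.

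- n per arm = (1.64 + 0.84)² × 2 × 0.75 × 0.25 / 0.15² × [1 + 23 × 0.005] = 6.1504 × 0.375 / 0.0225 × 1.115 = 114.29
- 114.29 / 0.95 = 120.3, which the plan states as 120, or 5 clusters of 24.

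The figure reproduces. It is built on a plain difference in recovery proportions, with nothing held fixed after allocation. That difference is what the margin refers to.

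**2. What the model estimates.** With P(recovery) = Φ(a + b·arm + c·stay), the arm difference on the probability scale is the average over children of Φ(a + b + c·stay) − Φ(a + c·stay). If recovery differs from non-recovery in stay (c ≠ 0) and the arms differ in stay, b absorbs part of that difference even when recovery is equal.

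**3. Illustration with equal recovery.** The protocol gives no distribution for stay, so these are assumptions: 25% SAM; recovery 60% in SAM and 80% in MAM (0.25 × 60 + 0.75 × 80 = 75%); mean stay 7 weeks if cured and 9 if not; SD 2.5; caps of 8 weeks (SAM) and 16 weeks (MAM); 300,000 children per arm. The true difference is zero, and a negative value makes the intervention look worse.

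| Shift in stay, intervention arm (before capping) | Difference without stay in model | Difference with stay in model |
|---|---|---|
| -2 weeks | about 0 | -9.1 points |
| -1 week | about 0 | -4.4 points |
| 0 | about 0 | 0.0 |
| +1 week | about 0 | +3.7 points |
| +2 weeks | about 0 | +6.7 points |

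The largest is 9.1 / 15 = 61% of the margin.

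**4. Illustration with a true deficit of 15 points (75% v 60%).** Assumptions: cure possible from week 4 at a constant hazard; uncured children leave early at a constant weekly rate. Without stay in the model the difference is about -15 throughout.

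| Early uncured exit per week | With stay, 16-week cap | With stay, 8-week cap |
|---|---|---|
| 0.2% | -5.0 | not given |
| 2% | -11.3 | not given |
| 3% | -13.5 | -14.0 |
| 4% | -16.8 | -15.9 |
| 5% | -20.2 | -19.1 |

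These are approximate: separate runs at 2% with the 16-week cap gave -11.3 to -12.6. The pattern is what matters. When most uncured children stay to the cap, adjustment shrinks the deficit. When many leave early, it enlarges the deficit. The crossover depends on the assumed timing of cure.

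**5. Admission severity, as a separate matter.** With balanced arms and a true effect, the simulated risk difference is -10.0 points with or without SAM/MAM in the model. The Probit coefficient moves only from -0.300 to -0.289 when severity is left out. With recovery of 60% and 80% as assumed above and no true effect:

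- SAM share 25% v 15%: (0.15 × 60 + 0.85 × 80) − (0.25 × 60 + 0.75 × 80) = 77 − 75 = 2 points.
- SAM share 35% v 15%: 77 − (0.35 × 60 + 0.65 × 80) = 77 − 73 = 4 points.

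Omission therefore shifts the result only if the SAM share differs by arm.

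**The case against.** The strongest reply is that recovery is tested first by a cluster-adjusted chi-squared test, which contains no length-of-stay term. The Probit is introduced afterwards, nothing calls it the deciding analysis, and the same section describes the quantitative analysis as mainly descriptive. This stands. A reader might infer that the plan could declare non-inferiority for an arm that is 15 points worse. That requires the Probit effect to be the quantity set against the margin, which the protocol does not say. It also requires the distortion to run towards zero, and step 4 shows that it can run the other way.

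A reader might also take stay to be almost a function of recovery. The exit rules do not support that, because uncured children can leave early through non-response or default. The link is partial, which is enough to spoil the coefficient but not enough to fix the direction.

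Finally, a reader might infer that leaving out admission severity or county biases the comparison. It does not in itself. The named list is open-ended, the clusters are randomised and pair-matched, and each county is to contribute to both arms. The shifts in step 5 rest on an assumed recovery gap and an assumed imbalance. What remains is a case for precision and protection: there are few clusters, and the sampling frame consists of cases diagnosed by CHVs, whose role differs by arm.

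None of this defends length of stay as a covariate. The protocol names it explicitly, so it is not a detail left to a later plan.

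**Conclusion.** The point holds for length of stay. As written, the Probit for recovery conditions on a post-allocation outcome that is partly determined by recovery, and its treatment coefficient should not be read as the effect of the intervention on recovery. That conclusion follows from the document alone.

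The size does not. Under the assumed scenarios the distortion is typically several percentage points against a 15-point margin. Its sign and size depend on how stay and early uncured exits differ by arm, and it can be zero. The chi-squared test is untouched, so the trial retains one valid route to an answer on this point. The protocol does not, however, say whether that test or the Probit decides non-inferiority. The absence of admission severity from the named covariates is a missed improvement and not an error of the same kind.

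**What to change.** - Remove overall length of stay from the recovery Probit and analyse it only as an outcome in its own right.
- State that covariates are restricted to values fixed before treatment starts.
- State which analysis of recovery is compared with the 15-point margin.
- As a lesser addition, name admission MUAC or SAM/MAM class as a baseline covariate. Because the intervention is expected to bring earlier case-finding, severity at admission may itself differ by arm in the endline cohort, so the adjusted result should be reported beside the unadjusted one.

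The cost is a few sentences in the analysis section. Admission severity is already recorded, no new data are needed, and the sample size stays at 120 per arm.
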